### Study endpoints and analyses

Our aim is to investigate the usability and acceptance of DECADE and determine whether improvements of the intervention, mode of implementation, study design, and endpoints are necessary for future evaluations.

To test our first study objective, the usability and acceptance of DECADE, we will analyze the qualitative data. This analysis will be performed by using the software MAXQDA (Version 11)[52]. All pseudonymized text material will be coded considering deductive categories (key questions of the patient questionnaire and the guideline-based GP interviews), and inductive categories (new aspects, if mentioned within the questionnaires or interviews). The text materials will be structured and validated by coding the interviewed person (patient or GP) and assigning positive, negative, or ambivalent validations of the categories in consideration of their context. The text analyses continue by counting the frequencies of evaluated codings [53, 54].

The second study aim, to test the feasibility of the study, will be reached by evaluating the study progress. This involves assessing the inclusion process, the randomization procedure, and the loss to follow-up of patients, as well as evaluating chosen instruments of the questionnaire, primary and secondary endpoints, and the analysis strategy.

The primary endpoint with regard to the third study aim is “patient activation,” as measured by a change in the PAM-13D score [44] between T0 and T1. The change in the PAM-13D score in the randomized groups and the potential effect of the intervention on this change will be estimated in a linear regression model with 95% confidence intervals, including as independent factors the intervention, GP practice, CVR score, and the PAM-13D score at T0. This will be done to facilitate sample size planning of the main trial.

Secondary endpoints with regard to the third study aim are the following: (1) The actual state of health, measured by a change in the EQ-VAS score [46] between T0 and T1. The potential effect will be estimated by linear regression including as independent factors the intervention, GP practice, CVR score, and EQ-VAS score at T0. The outcomes (2) change of health behavior [48], (3) the usefulness of patient material (USE) [51], (4) the adapted Goal Attainment Scaling (GAS) [49, 50], and (5) the satisfaction with goal attainment (own development) will be analyzed descriptively by the comparison of mean scores in T1.

Due to the randomization at the patient level, we can assume that sociodemographic and clinical data will be evenly distributed between the DECADE group and the Arriba group. Nevertheless, we will describe potential differences between both groups regarding age, gender, educational level, and occupational status, as well as health status (clinical data and patient reported outcomes) at baseline. The relationship of baseline characteristics with the primary endpoint patient activation (PAM-13D) will be described. Potential factors identified as prognostic will be considered in the planned multi-center trial. Additionally, the change in the clinical data of SBP, total and HDL cholesterol, body mass index (BMI), HbA1C, and CVR score will be analyzed descriptively by the change of mean values between T0 and T1.

Before carrying out the analyses, possible missed patterns will be explored (frequencies as well as relationship to patient characteristics and outcome measurements). If necessary, single items have to be excluded from the analyses. Imputation is not planned in this pilot study.

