**Fig. 1 Fig1:**
[figure not shown]
Flowchart of the DECADE pilot study. *GP* general practitioner, *MA* medical assistant, *CVR* cardiovascular risk. *One asterisk* indicates target numbers. *Double asterisks* indicate estimated numbers

*Randomization of the patients* will be carried out by GPs after CVR calculation using prepared, sealed randomization envelopes. Randomization envelopes are prepared by the Clinical Trials Unit of the University Medical Center Freiburg for concealment of randomization. Randomization was stratified by GP practice, with half of the patients assigned to the DECADE group and half of the patients to the Arriba group. GPs do not know the result of the randomization before they open the randomization envelopes to avoid selection bias. Blinding during the intervention is not possible because (1) the GPs use the DECADE booklets together with their patients, (2) MAs distribute the patient questionnaires which differ in T1 according to the study group, and (3) patients are informed about the waiting list control design.

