#### Patient questionnaires

The baseline assessment (T0) includes the following data:Subjective quality of life (Visual Analogue Scale of the EQ-5D (EQ-VAS)) [46]Height and weightSelf-rated risk factors like smoking, overweight, unhealthy diet, lack of physical activity, stress, and alcohol (Indicators of the Rehabilitation Status (IRES)) [47]Patient activation measure (German 13-item version; PAM-13D). It assesses patient knowledge, skills, confidence, and behavior critical for coping with a chronic illness [44].Sociodemographic data: gender, age, family status, educational level, occupational status, and extent of gainful employment

In the follow-up assessment (T1), the same data are collected as in the baseline assessment (except for sociodemographic data). In addition, the following are assessed:Changes in health behavior [48],Adapted Goal Attainment Scaling (adapted GAS) [49, 50] and satisfaction with goal attainment (our own development). On the adapted GAS, patients mark their individual treatment goals (such as various lifestyle changes, regular blood pressure or blood glucose measurements at home, or regular intake of medication as prescribed) and rate whether they attained their goals on a scale from 0 (not attained at all) to 5 (better attained than I planned). The structure of the second scale (satisfaction with goal attainment) corresponds to the adapted GAS, but patients rate their satisfaction with goal attainment from 1 (very satisfied) to 4 (very unsatisfied).The usefulness scale for patient information (USE) [51],Satisfaction with consultation and support by the GP (our own development). This instrument includes six items, specifically on (1) the GP’s consultation on the individual CVR, (2) agreement on treatment goals, (3) communication about treatment plans or behavior changes, (4) communication about success and failure, (5) shared search for solutions in case of problems, and (6) motivation by the GP. Patients rate their satisfaction on a scale from 1 (very satisfied) to 4 (very unsatisfied).

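### Secondary endpoints 2 to 5 are compared as plain T1 means, without the practice strata used in randomisation and with no interval named; a modest loss, cheaply repaired

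*Protocol article*

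**What the plan says.** In Study endpoints and analyses, secondary endpoints 2 to 5 (change of health behaviour, USE, adapted goal attainment scaling, satisfaction with goal attainment) "will be analyzed descriptively by the comparison of mean scores in T1". No stratum, covariate or interval is named.

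The same section treats two other endpoints differently. For the change in PAM-13D, the analysis reads: "linear regression model with 95% confidence intervals, including as independent factors the intervention, GP practice, CVR score, and the PAM-13D score at T0". EQ-VAS, which is secondary endpoint 1, has this analysis: "linear regression including as independent factors the intervention, GP practice, CVR score, and EQ-VAS score at T0".

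The randomisation paragraph under Fig. 1 states: "Randomization was stratified by GP practice, with half of the patients assigned to the DECADE group". Under Patient questionnaires, the instruments for endpoints 2 to 5 are listed as additions at T1, so they have no T0 value. The Sample size calculation section expects 34 analysed patients per arm, reports no formal calculation, and says that the quantitative analyses should still let trends be seen.

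**The concern.** Practice is part of the design: the randomisation is stratified by it, and two models in the plan respect it. It may also matter for the outcomes left out, because goals are set and reviewed with the patient's own GP and two of the four scales rate those goals. The analysis therefore follows the design for PAM-13D and EQ-VAS and not for the other four endpoints, and the article gives no reason.

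What is at stake is how the numbers will be read. These endpoints serve the third aim, initial data on the potential effects of DECADE, and the quantitative results feed the judgement of whether the intervention is promising. A gap between two means of about 34 patients, shown without an interval, is easily taken for one of the expected trends.

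**Working it through.** **Inputs.** From the Sample size calculation section: 84 patients (42 per arm), 20% loss, 34 analysed per arm, PAM-13D SD 15, stated precision about 5. From Design and setting: six practices. The article gives no SD for endpoints 2 to 5, so results are in SD units. It gives no intraclass correlation (ICC) for practice, so 0 to 0.20 is an assumed range.

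**1. The plan's own figures.** 84 × 0.8 = 67.2, against 68 stated: agrees within rounding to equal arms. Half-width for one arm's mean: 1.96 × 15 / √34 = 5.04, which reproduces the stated 5. It describes a single arm. For the difference between arms the same inputs give 1.96 × 15 × √(2/34) = 7.13.

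**2. Uncertainty of a T1 mean difference.** SE = √(2/34) = 0.243 SD. The 95% half-width is 1.96 × 0.243 = 0.475 SD (normal), or 0.484 SD with t on 66 degrees of freedom: about 0.48 SD. With no true effect, a gap above 0.25 SD in either direction has probability 2 × [1 − Φ(0.25/0.243)] = 0.30.

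**3. Effect of leaving practice out.** Simulation: six practices of 14 patients, randomised 7:7 within practice, each patient retained at random with probability 68/84, no treatment effect, total variance 1, 8000 runs per ICC. The adjusted model holds intervention and practice only.

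| Assumed ICC | Mean half-width, raw (SD) | Mean half-width, practice in model (SD) | Change | Coverage of raw interval |
|---|---|---|---|---|
| 0 | 0.483 | 0.487 | 0.9% wider | 95.1% |
| 0.01 | 0.483 | 0.485 | 0.5% wider | 94.8% |
| 0.05 | 0.482 | 0.476 | 1.3% narrower | 95.4% |
| 0.10 | 0.481 | 0.464 | 3.6% narrower | 96.2% |
| 0.20 | 0.475 | 0.436 | 8.2% narrower | 96.6% |

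The mean raw difference stayed within 0.007 SD of zero at every ICC, so there is no sign of bias.

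The gain lies in the interval more than in the estimate. The actual spread of the estimated difference hardly changes (0.230 raw against 0.229 adjusted at ICC 0.10; 0.220 against 0.218 at 0.20), because stratified allocation has already removed most of the practice variation from the comparison. The raw analysis does not credit this and overstates its own standard error.

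**The case against.** The case for leaving the text alone has weight. Endpoints 2 to 5 are measured only at T1, so a baseline-adjusted change model of the PAM-13D kind is not available and T1 means are the natural summary. The analysis is called descriptive, in a pilot with no formal sample size, and no test or decision rule rests on it. The article does not say that intervals will be withheld; it names none, and a fuller document may supply them. The numerical harm from omitting practice is small and conservative in direction.

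Most of this stands, and it limits the weight of the point. It does not remove it. A model with practice and CVR score needs no T0 value of the outcome, and both terms are already used in the same section. The choice of raw T1 means is a stated analysis, not an unstated detail. The interval is the weaker part of the criticism, since it rests on silence.

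Three stronger readings are tempting, and the article does not support them.

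- A reader might infer that raw means were chosen because randomisation is trusted to balance the arms, since the article writes that "we can assume that sociodemographic and clinical data will be evenly distributed between the DECADE group and the Arriba group". That sentence introduces the baseline comparison, is never given as a reason for the analysis of endpoints 2 to 5, and is qualified at once: "Nevertheless, we will describe potential differences between both groups regarding age, gender, educational level, and occupational status".
- A reader might infer that unequal losses across practices bias the raw comparison. Losses that differ between practices but are alike in both arms do not. Bias by this route needs loss that differs by arm within practices. The Data management rule on shared households does remove only Arriba patients, but nothing in the article shows that removals would be large enough to matter, and the simulation used random loss only.
- A reader might expect the adjusted model to deal with chance imbalance in general. It would contain practice, CVR score and perhaps PAM-13D, not age, gender, education or occupation.

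**Conclusion.** The point holds as a modest improvement to the analysis; it does not expose an error in the results the plan would produce. Endpoints 2 to 5 are planned without the randomisation strata, unlike PAM-13D and EQ-VAS. Under random loss this leaves the comparison unbiased, and raw intervals would cover about 95% to 97%.

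The larger practical gain is the interval. A half-width near 0.48 SD, which follows from 34 per arm alone, shows the reader how little a gap of 0.25 SD means. Adjustment does not cure that imprecision. The gain from the practice term depends wholly on the assumed ICC: nothing at 0, about 4% off the half-width at 0.10, about 8% at 0.20. Any further gain from CVR score was not evaluated.

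**What to change.** For each of endpoints 2 to 5, keep the raw T1 means by arm and add the DECADE-Arriba difference with a 95% confidence interval from a linear model with intervention, GP practice and T0 CVR score. T0 PAM-13D may be added, but the article does not show that it predicts these outcomes. Label the estimates exploratory, with no conclusion on effectiveness drawn from them.

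Cost: one sentence in the analysis section and four model runs on data already collected. Against a two-mean comparison, practice takes 5 degrees of freedom and CVR score 1, so 6 of about 68, or 7 with PAM-13D. If practices do not differ, the practice term widens the interval by about 1%.

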**Methods:**

This randomized controlled pilot trial will generate initial data on the potential effects of DECADE on patients’ self-evaluated activity and behavior change as well as on clinical outcomes such as blood pressure, cholesterol, body mass index (BMI), HbA1C, and CVR score. In the qualitative part of the study, we will analyze data collected in semi-structured interviews with participating general practitioners (GP) and in patient questionnaires.

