To assure a random sample of the patients in each GP practice, medical assistants (MAs) of the practices are asked to apply a structural recruitment procedure: MAs check the electronic medical records (EMR) of adult patients who are scheduled during two morning hours of 2 days and two afternoon hours of a third day in a week regarding CVR factors. If at least one of the abovementioned CVR factors is found in the EMR and if those patients fulfill the inclusion criteria, they will be informed about the study. If they are willing to take part in the study, they sign the study’s informed consent form. The GP practices are instructed not to recruit patients who live in the same household to prevent a contamination of the control group.

Included patients fill out the baseline questionnaire (T0). In order to calculate the CVR with Arriba, MAs take a blood sample to determine necessary laboratory values (total and HDL cholesterol, and in the case of diabetes HbA1c) and perform a standardized blood pressure measurement (mean of three measurements after a 5-min resting period) of all patients. A few days later, the GPs use the Arriba calculator to calculate the CVR and consult the patients regarding reasonable treatment options and the effect on the absolute individual CVR. All patients receive the printed Arriba form that contains clinical data, treatment options, and actual and potential CVR scores. The recruitment procedure and details of the T0 data assessment are presented in Fig. 1.

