## Discussion

Main objectives of this pilot study are (1) to test the new intervention DECADE in terms of its usability and acceptance in primary care, (2) to test the feasibility of the study design and analysis strategy, and (3) to generate initial data on the potential effects of the DECADE intervention compared to the Arriba intervention.

We will take into account potential selection bias regarding patient age, gender, and CVR factors. Therefore, we will compare these characteristics of invited but non-participating patients versus included patients. The anonymized data of non-participants will be assessed by the MAs and submitted to the project team of DECADE pilot.

The comprehensive evaluation of the DECADE pilot study will combine the results of the quantitative and qualitative analyses and will indicate whether DECADE is a promising intervention in the domain of patient-centered prevention of CVD. We will use the results to refine the DECADE intervention and the planned multi-center randomized controlled trial.

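### Clinical outcomes get only a descriptive T0 to T1 change in means, with no baseline-adjusted DECADE-versus-Arriba estimate or interval

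*Protocol article*

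**What the plan says.** The protocol article, under Study endpoints and analyses, states that the clinical outcomes "will be analyzed descriptively by the change of mean values between T0 and T1". The outcomes it covers in this way are listed as "the change in the clinical data of SBP, total and HDL cholesterol, body mass index (BMI), HbA1C, and CVR score". That is the whole plan for these outcomes. No model, contrast between arms, interval or baseline covariate is named for them there or elsewhere in the article.

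The same section treats two questionnaire outcomes differently. PAM-13D and EQ-VAS each get a linear regression on intervention, GP practice, CVR score and the outcome's own T0 value. For PAM-13D, 95% confidence intervals are named as well.

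The aims include the clinical outcomes. The Methods paragraph of the abstract announces initial data on potential effects on activation and behaviour "as well as on clinical outcomes such as blood pressure, cholesterol, body mass index (BMI), HbA1C, and CVR score". The last paragraph of Background also lists clinical outcomes. The Discussion makes the aim comparative: "to generate initial data on the potential effects of the DECADE intervention compared to the Arriba intervention".

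The baselines exist. Under Study population and recruitment procedure, "MAs take a blood sample to determine necessary laboratory values (total and HDL cholesterol, and in the case of diabetes HbA1c". For blood pressure, the same staff "perform a standardized blood pressure measurement (mean of three measurements after a 5-min resting period) of all patients". Height and weight are in the T0 questionnaire, and the CVR is calculated at T0. All of these are planned again at month 4.

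**The concern.** The control arm is active. According to Design and setting and to Intervention, both arms have their risk and treatment effects calculated with Arriba, set goals with the GP after a week, and review progress on the same timetable. DECADE adds the booklets and the website access. The change from T0 to T1 in the DECADE arm therefore contains the effect of Arriba, of the shared consultations, of time, and of regression to the mean in patients selected for a risk factor. Only a comparison with the Arriba arm separates out what DECADE adds.

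A reader could subtract one arm's change from the other's, but that difference would have no interval and no correction for unequal starting values. The section says that, because of randomization, "we can assume that sociodemographic and clinical data will be evenly distributed between the DECADE group and the Arriba group". Randomization gives balance on average; in one trial of this size, sizeable chance differences are ordinary. At stake is how usable the clinical data are when the main trial is designed. The estimates would be noisier than they need to be, and their uncertainty would not be shown.

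**Working it through.** **Inputs from the article (Sample size calculation).** 84 patients taking part, 42 per arm; 20% loss to follow-up; analysis sample 68, or 34 per arm.

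**The plan's own figures.** 42 × 0.80 = 33.6, rounded to 34 per arm, gives 68. The stated precision of about 5 for PAM-13D is reproduced as 1.96 × 15/√34 = 5.04, the half-width for the mean of one arm. It concerns PAM-13D only. The article gives no SD or precision for any clinical outcome, so the results below are in SD units.

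**Assumptions.** Equal SDs at T0 and T1, and a T0-T1 correlation r that the article does not give, shown from 0.3 to 0.9. Large-sample formulas are used, ignoring the small cost of estimating the slope and the practice terms.

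**Step 1: chance imbalance at baseline.** The SD of the difference in T0 means is √(2/34) = 0.243 SD. Its 95% range is ±1.96 × 0.243 = ±0.48 SD.

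**Step 2: what that does to a difference in change.** If T1 depends on T0 with slope r, the change T1 − T0 depends on T0 with slope r − 1. An imbalance d then shifts the unadjusted difference in change by (r − 1)d. For d = 0.475 and r = 0.5 this is −0.5 × 0.475 = −0.24 SD: the arm that starts higher appears to fall more.

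**Step 3: variance.** In units of the outcome variance, the change score has 2(1 − r) and the T0-adjusted outcome has 1 − r². Their ratio, adjusted to change, is (1 + r)/2.

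**Step 4: half-width of the 95% CI for the difference between arms.** This is 1.96 × √(2V/34), where V is the variance from step 3.

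| r (assumed) | V, change | V, adjusted | Variance saved | Half-width, change | Half-width, adjusted | Size of shift at 0.48 SD imbalance |
|---|---|---|---|---|---|---|
| 0.3 | 1.40 | 0.91 | 35% | 0.56 | 0.45 | 0.33 |
| 0.5 | 1.00 | 0.75 | 25% | 0.48 | 0.41 | 0.24 |
| 0.7 | 0.60 | 0.51 | 15% | 0.37 | 0.34 | 0.14 |
| 0.9 | 0.20 | 0.19 | 5% | 0.21 | 0.21 | 0.05 |

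Half-widths and shifts are in SD units. With T0 in the model, regressing the T1 value or the change gives the same intervention coefficient, so the form already used for PAM-13D carries over.

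**The case against.** The strongest reply is that this is a pilot and a descriptive analysis is a legitimate choice. The clinical outcomes are neither the primary endpoint nor among the five numbered secondary endpoints. The abstract's third objective asks only whether changes can be observed, and the sample size section expects only trends. This stands as to weight: the point is modest. It does not remove the mismatch with the comparative aim, and an estimate with an interval and no test is still descriptive.

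It is also fair that adjustment gains little where the correlation is high. That is plausible for BMI over four months and for a CVR score built partly on fixed characteristics such as age and gender.

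Several stronger readings are tempting, but the article does not support them:

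- **That drop-out will create a spurious change.** This needs the T0 mean to include patients who have no T1 value. The wording does not say so, and paired data fit it equally well. If the means were unpaired, and the 20% lost had started 10 mmHg above those who stayed (an assumption), the mean would fall 0.20 × 10 = 2 mmHg with no patient changing. With pairs this artefact disappears.
- **That ±0.48 SD is the error in the planned quantity.** A change score already subtracts T0. The relevant shift is the last column of the table.
- **That imbalance is ignored.** The sentence after the one on even distribution says that baseline differences between the groups will be described. Describing them does not correct the outcome comparison, but they are not overlooked.
- **That results by arm are excluded.** They are not. What is missing is the adjusted contrast and its interval.
- **That the pilot breaks a promise of residual SDs for clinical outcomes.** No section makes one. The article ties sample size planning to the PAM-13D model only.
- **That outcomes which "will be analyzed descriptively by the comparison of mean scores in T1" share the defect.** The health behaviour scale is listed among the measures added at T1, so it has no T0 value to adjust for.

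**Conclusion.** The point holds in a limited form. The stated analysis of the clinical outcomes provides no baseline-adjusted estimate of DECADE against Arriba and no interval, although the aim is comparative, the control is active and the T0 values are at hand. This is an analysis the article states, not a detail left to another document.

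The gain in precision is useful at low to moderate correlation and negligible near 0.9. Even after adjustment, the half-width stays at 0.34 to 0.45 SD for correlations of 0.7 down to 0.3, so the estimates will be imprecise. These sizes rest on equal SDs, on the expected 34 per arm and on assumed correlations. The argument that a within-arm change cannot isolate DECADE rests on none of these. The primary endpoint and the feasibility aims are unaffected.

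**What to change.** For systolic blood pressure, total and HDL cholesterol, BMI and CVR score, use the kind of regression already planned for PAM-13D: the T1 value, or the change, on intervention, GP practice and the outcome's own T0 value, in patients with both measurements. Report the adjusted difference between arms with its 95% CI, labelled exploratory and without a test. State that means and changes by arm come from the same paired patients.

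HbA1c is measured only in patients with diabetes, whose number is not stated, and a model with six practices may not be estimable. Adjust for arm and T0 value if numbers allow; otherwise report paired changes by arm.

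The cost is a few more regressions on data already being collected, with no added patients or visits. The downside is several wide exploratory intervals, which should not be read as evidence for or against an effect.
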